**Please refer to the Laboratory Manual for detailed processing and shipping instructions.**

Label all specimens with the following:

1. Subject initials
2. Subject study number (will include protocol number)
3. Visit at which sample was drawn (i.e. C1D4)
4. Date sample drawn (i.e. mm/dd/yyyy)
5. Time sample drawn (24-hour clock)
6. Sample type (e.g. plasma, serum, bone marrow cells, tumor cells)

Shipping Instructions in the US:

1. An inventory sheet including a complete list of samples shipped (patient number, time point, study #) must accompany each shipment.
2. An electronic copy (Word or Excel) of the sample list must also be sent via email. The listing must also include a contact name, address and phone number of the person who is responsible for the shipment. They should sign and date the form.
3. Please contact lab technician to alert him/her of an incoming shipment by email:

[REDACTED]

[REDACTED]

[REDACTED]

[REDACTED]

[contact]

Note: Please follow your institution's policy regarding destruction of patient samples upon withdrawal of informed consent.

## **8 ADVERSE EVENTS**

An AE is any untoward medical occurrence in a study subject administered an investigational product and that does not necessarily have a causal relationship with this treatment.

An AE therefore can be any unfavorable and unintended sign (including laboratory finding), symptom or disease temporally associated with participation in an investigational study, whether or not considered drug-related. In addition to new events, any increase in the severity or frequency of a pre-existing condition that occurs after the subject signs a consent form for participation is considered an AE. This includes any side effect, injury, toxicity, or sensitivity reaction.

An unexpected AE is any adverse drug event, the specificity or severity of which is not consistent with the current IB or prescribing information for a marketed compound. Also, reports which add significant information on specificity or severity of a known, already documented AE constitute unexpected AEs. For example, an event more specific or more severe than described in the IB would be considered "unexpected".

Whenever possible, the Common Terminology Criteria for Adverse Events (CTCAE) version 4.0 should be used to describe the event and for assessing the severity of AEs (see [Appendix 3](#)). Any events representing a change in the CTCAE grade need to be reported on the AE case report form. This includes any change in laboratory values.

For AEs not adequately addressed in the CTCAE, the severity table below may be used:

| Severity                      | Description                                                                                                                                                                                               |
|-------------------------------|-----------------------------------------------------------------------------------------------------------------------------------------------------------------------------------------------------------|
| GRADE 1 – Mild                | Transient or mild discomfort; no limitation in activity; no medical intervention/therapy required.                                                                                                        |
| GRADE 2 – Moderate            | Mild to moderate limitation in activity—some assistance may be needed; no or minimal medical intervention/therapy required.                                                                               |
| GRADE 3 – Severe              | Marked limitation in activity, some assistance usually required; medical intervention/therapy required, hospitalizations possible.                                                                        |
| GRADE 4 –
Life-threatening | Extreme limitation in activity, significant assistance required; life-threatening (immediate risk of death); significant medical intervention/therapy required, hospitalization or hospice care probable. |
| GRADE 5 – Fatal               | Death                                                                                                                                                                                                     |

Any condition, laboratory abnormality, or physical finding with an onset date prior to the subject signing consent for study participation is considered to be pre-existing in nature and part of the subject's medical history.

## 8.1 Causality

Using the following criteria, the relationship of the AE to the study drug should be assessed as follows:

Definite (5) – The AE *is clearly related* to the study treatment.

Probable (4) – The AE *is likely related* to the study treatment.

Possible (3) – The AE *may be related* to the study treatment.

Unlikely (2) – The AE *is doubtfully related* to the study treatment.

Unrelated (1) – The AE *is clearly NOT related* to the study treatment.

All AEs will be considered for dose-limiting toxicity evaluation unless the event can clearly be determined to be unrelated to the drug.

## **8.2 Adverse Event Reporting Procedures**

Information about all AEs, whether volunteered by the subject, discovered by the treating investigator questioning, or detected through physical examination, laboratory tests or other means, will be collected and recorded in eVelos and followed as appropriate.

All adverse events **must** be reported in routine study data submissions to the Lead PI who will review and will be responsible for alerting all participating sites about the AE as required. **AEs reported using the Serious Event Reporting Form and/or MedWatch Form discussed below must also be reported in routine study data submissions in eVelos.** Details of the event must include severity, relationship to study drug, duration, action taken, and outcome as shown on the eCRF in eVelos. All AEs must be followed to resolution or stabilization regardless of relationship to study drug.

All AEs that are considered related to study regimen must be followed to resolution or stabilization if improvement is not expected.

AEs must be reported from the date the subject signs consent through 30 days post-last dose of study treatment or initiation of a new anticancer therapy, whichever occurs first. If a subject is enrolled but discontinues study prior to receiving any study drug, only SAEs that are considered related to study procedures must be reported through the end-of-study visit. AEs that completely resolve and then recur should be recorded as a new AE. For subjects who complete the end of study visit less than 30 days following their last dose of study drug, a follow up of ongoing AEs should be attempted by telephone, and documented in the subject's source. AEs continuing at 30 days post-last dose should have a comment in the source by the treating investigator that the event has stabilized or is not expected to improve. SAEs continuing at 30 days post-last dose should be followed until resolution or stabilization.

The treating investigator is responsible for evaluating all AEs for relationship to study drug and for seriousness, obtaining supporting documents, and determining that documentation of the event is adequate. Adverse events will be assigned a severity grade using the NCI-CTCAE grading scale v4.0. The

treating investigator must assess all abnormal laboratory results for their clinical significance. Only Grade 1 and 2 abnormal laboratory values that are clinically significant, related to study treatment, and/or requiring concomitant medication will be recorded. If any abnormal laboratory result is considered clinically significant, the treating investigator must provide details about the action taken with respect to the test drug and about the patient's outcome. All Grade 3 and 4 laboratory abnormalities must be recorded as AEs on the CRF. Grade 1 and 2 abnormalities should only be recorded if they require treatment or are otherwise considered clinically significant by the treating investigator.

The Lead Principal Investigator may delegate these duties to sub-investigators and must ensure that these sub-investigators are qualified to perform these duties under the supervision of the Lead Principal Investigator, and that they are listed on the delegation log.

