### **10.2.3 Secondary Endpoint Analysis**

The rate of MRD-negative disease by NGS will be reported at screening, 8, 12, 18, 24 months and then yearly until progression up to 5 years. Additionally, sites will be required to provide unstained pre-treatment slides to assess MRD by Adaptive. Comparison between D+KRd and historical KRd+ASCT rates will be made using a standard chi-square or Fisher's exact test. At the conclusion of the trial, with all subjects evaluated for PFS assessment at 5-years, the rate of MRD-negative status will be compared between D+KRd and historical KRd+ASCT data. This analysis will be conducted by contingency tables, or by adjusted logistic regression models, which will explore for any important confounders. Improvement of response during therapy measured at 6 and 12 months first treatment on protocol will be compared between D+KRd and historical KRd+ASCT data. Proportions of improving patients will be reported by treatment group, and comparisons of those proportions will be conducted using the chi-square or Fisher's exact tests. Overall survival will be calculated from date of first treatment on protocol until death from any cause and measured based upon the intention-to-treat paradigm, and will be compared between D+KRd and historical KRd+ASCT data using Kaplan and Meier survival models and the log-rank test statistic. In addition, all secondary endpoints will be tested for differences to historical controls using the one-sample log-rank test. The duration of MRD-negative disease will be calculated between the date of first occurrence of MRD-negative status, until such time as MRD-positive disease assessment or date of disease progression. Comparisons of duration of MRD-negative status may require the use of interval censoring methods. And finally, safety of the regimens will be assessed by comparing CTCAE Grade toxicity occurrence between D+KRd and historical KRd+ASCT data. Toxicity of Grade 2 and higher will be tabulated for each system organ class (SOC) and common individual toxicities occurring with SOC's reported. The maximum graded toxicity overall and within SOC will be reported per patient with the results summarized by treatment group and frequencies compared using chi-square tests or Fisher's exact tests as appropriate.

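### Conflicting recording rules for Grade 1-2 laboratory abnormalities leave the planned Grade 2+ toxicity table, and its comparison with historical KRd+ASCT, resting on incomplete and inconsistent counts

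*Protocol*

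**What the plan says.** Three places in the protocol bear on this.

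**The analysis.** Section 10.2.3 states that "safety of the regimens will be assessed by comparing CTCAE Grade toxicity occurrence between D+KRd and historical KRd+ASCT data". The threshold follows: "Toxicity of Grade 2 and higher will be tabulated for each system organ class (SOC" category. On the summary measure it says "The maximum graded toxicity overall and within SOC will be reported per patient", with frequencies compared by chi-square or Fisher's exact test.

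**The general recording rule.** Section 8 states: "Any events representing a change in the CTCAE grade need to be reported on the AE case report form". The next sentence extends this to the laboratory: "This includes any change in laboratory values".

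**The laboratory recording rule.** Section 8.2 narrows this in two sentences of one paragraph. The first reads: "Only Grade 1 and 2 abnormal laboratory values that are clinically significant, related to study treatment, and/or requiring concomitant medication will be recorded". The second, at the end of the paragraph, reads: "Grade 1 and 2 abnormalities should only be recorded if they require treatment or are otherwise considered clinically significant by the treating investigator". Between them stands an unconditional rule for severe values: "All Grade 3 and 4 laboratory abnormalities must be recorded as AEs on the CRF".

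The protocol does not say which of the three low-grade sentences prevails. Section 10.2.3 does not say whether laboratory toxicity is counted from adverse event forms or from graded laboratory results.

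**The concern.** A table that starts at Grade 2 needs Grade 2 events to be captured by one rule. Here the Grade 2 laboratory part is either fully captured (Section 8) or filtered by judgment (Section 8.2), and the filter has two versions. With 4 to 6 centers (Section 4.1.1), sites acting in good faith could follow different sentences.

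The comparator is external, and the protocol does not state how its low-grade laboratory values were recorded. A gap in Grade 2+ frequency between D-KRd and KRd+ASCT could then come from what was written down rather than from what the drugs did. Cytopenias are laboratory findings. Section 1.7 reports more neutropenia when daratumumab was added in one randomized trial, and more neutropenia and thrombocytopenia in another. The same adverse event records go to the data and safety monitoring board, which weighs toxicity against historical KRd experience (Sections 13.6.1 and 13.6.2).

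**Working it through.** **Step 1: apply the three sentences to the same value.** Take a new Grade 2 laboratory value, so that the CTCAE grade has changed. Read the list in the first Section 8.2 sentence as alternatives, any one of which suffices.

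| Grade 2 laboratory value | Section 8 | Section 8.2, first sentence | Section 8.2, last sentence |
|---|---|---|---|
| Needs treatment | recorded | recorded | recorded |
| Untreated, judged clinically significant | recorded | recorded | recorded |
| Untreated, treatment-related, judged not significant | recorded | recorded | **not recorded** |
| Untreated, unrelated, judged not significant | recorded | **not recorded** | **not recorded** |

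The third row is the important one. An asymptomatic, drug-related cytopenia that needs no treatment is counted under two sentences and missed under the third, and two of the three stand in the same paragraph. Grade 3-4 laboratory values are recorded under every rule. Grade 2 clinical events are not touched by the laboratory restriction.

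**Step 2: what the counts would then measure.** The protocol states no figure here to reproduce. Let g3 be the share of patients whose worst laboratory grade is 3 or more, g2 the share whose worst is exactly 2, and s the share of those Grade 2 patients who reach the form. Then:

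- true Grade 2+ laboratory rate = g3 + g2
- recorded rate = g3 + s × g2
- shortfall = (1 − s) × g2

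The documents give none of these three quantities, so the figures below only illustrate. With n = 45, g2 = 30% and g3 = 30%, the true rate is 60%, or 27 of 45:

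| s | Recorded rate | Of 45 |
|---|---|---|
| 100% | 0.30 + 1.00 × 0.30 = 60% | 27.0 |
| 75% | 0.30 + 0.75 × 0.30 = 52.5% | 23.6 |
| 50% | 0.30 + 0.50 × 0.30 = 45% | 20.3 |
| 25% | 0.30 + 0.25 × 0.30 = 37.5% | 16.9 |

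Over an assumed range of g2 from 20% to 40% and s from 25% to 100%, the shortfall runs from 0 to (1 − 0.25) × 0.40 = 30 percentage points.

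**Step 3: what happens in the historical comparison.** Suppose D-KRd and KRd+ASCT have the same true rates, with recording shares s(D) and s(H). The apparent difference is (s(D) − s(H)) × g2. With g2 = 30%:

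- s(D) = 50%, s(H) = 100%: −15 points, so D-KRd looks safer.
- s(D) = s(H): 0 points.
- s(D) = 100%, s(H) = 50%: +15 points, so D-KRd looks more toxic.

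For scale, take the first direction with full historical recording, an assumed 53 historical patients, g2 = g3 = 30% and a two-sided 5% test. The chance of a spurious finding of lower toxicity is about 3%, 11%, 31% and 61% at s(D) = 100%, 75%, 50% and 25%. These figures depend on every one of those assumptions.

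**The case against.** Several points on the other side have weight.

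- **Filtering low-grade laboratory values by clinical significance is acceptable in itself.** This stands. The defect is pairing a filter, stated in two versions, with an opposite rule in Section 8 and a table that starts at Grade 2.
- **Section 8 could be read as asking only that grade changes of events already recorded be updated**, with Section 8.2 as the specific laboratory rule. That would soften the first conflict, though the added sentence on laboratory values sits badly with it. It would not resolve the conflict inside Section 8.2.
- **The table may not be built from adverse event forms.** The Synopsis also lists laboratory safety evaluations, Section 10.2.3 names no source, and derivation rules may sit in an analysis plan not shown. The protocol does, however, define the safety endpoint by adverse event frequencies (Section 3.2) and summarizes adverse events by type, grade and attribution (Section 10.2.2). The point is therefore conditional: it concerns counts taken from the forms.
- **Central oversight limits site variation.** The lead investigator reviews all adverse events (Section 8.2), one institution trains affiliate sites (Section 13.4.3) and it monitors all sites (Section 13.5). This may help, but oversight cannot enforce a rule the protocol has not settled.
- **The severe events are safe.** Cytopenias of special interest start at Grade 4 (Section 8.3, Janssen reporting), and all Grade 3-4 laboratory values are recorded. This stands and limits the stakes.

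A reader might go further and infer that the Grade 2+ counts are simply wrong, that a large and calculable share of the 45 patients is lost, or that D-KRd will be made to look safer. The documents support none of these. They give no Grade 2 rates. The relatedness trigger in the first Section 8.2 sentence would admit many of the cytopenias in question. A shortfall for a single laboratory term does not carry over to maximum grade within an organ class, because a patient with a Grade 3-4 event in that class is unaffected. The direction depends on a historical recording rule that is not stated. If that rule matched, the shortfall would be shared.

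**Conclusion.** The conflict is established from the text. Sections 8 and 8.2 give incompatible instructions for Grade 1-2 laboratory values, and Section 8.2 disagrees with itself on whether relatedness to treatment is enough. If the Grade 2+ table in Section 10.2.3 is filled from adverse event forms, its laboratory part is incompletely and inconsistently recorded, and the comparison with historical KRd+ASCT may reflect recording practice rather than drug.

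The effect is confined to Grade 2 laboratory abnormalities in a secondary safety analysis. Its size and direction cannot be derived from the documents. The 0 to 30 point range and the spurious-result probabilities rest on assumed values. The matter should be corrected, because the instructions go to sites and the analysis they feed is a planned comparison.

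**What to change.** 1. **Sections 8 and 8.2.** Adopt one recording rule for Grade 1-2 laboratory values, stated once. Say whether relatedness alone triggers recording, and make Section 8 refer to that rule.
2. **Section 10.2.3, D-KRd table.** Derive laboratory toxicity of Grade 2 and higher by CTCAE v4.0 grading of the scheduled hematology and chemistry results, taking the worst grade per patient. State how a grade already present at baseline is handled. Keep adverse event forms as the source for clinical events.
3. **Section 10.2.3, historical comparison.** Limit the laboratory comparison with KRd+ASCT to Grade 3 and higher unless the historical laboratory data can be graded the same way. Grading one side only would create a new mismatch.

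The cost is small. The results are already scheduled (Section 6.1.2, Appendix 8), and on-treatment assessments are already entered in the study database (Section 5.3.1). It takes one programming step and a few sentences. Two things are given up: Grade 2 laboratory frequencies may look less favourable, and the historical comparison may lose its Grade 2 laboratory component.

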### **8.3 Serious Adverse Events**

Information about all serious adverse events (SAE) will be collected independently.

All SAEs from US sites will be collected by the UC CRA and reviewed by the Lead Principal Investigator. Only those determined to be SUSARs by the Lead Principal Investigator will be distributed to all participating sites (using the completed MedWatch 3500 form). To ensure patient safety, each serious adverse event occurring in the US must be reported to the Lead Principal Investigator and he or a designee will in turn, report to the University of Chicago Comprehensive Cancer Center via entry on the SAE eCRF in eVelos within 24 hours of learning of its occurrence. In the event that direct entry into eVelos is not available, a paper SAE form is provided for this study and may be used and sent via fax or email.

The Lead Principal Investigator is responsible for notifying the ethics committees (ECs), and investigators, of any expedited, annual, or other periodic safety reports in accordance with applicable regulations.

The Site Investigator is also responsible for notifying the local ECs in accordance with local regulations. Additionally, the Lead Principal Investigator is responsible for reporting SAEs to Amgen and Celgene as described in Section 8.4.

#### **8.3.1 Serious Adverse Event Definition**

An SAE is one that meets the following criteria:

- Results in death
- Life-threatening experience defined as any adverse experience that places the subject, in the view of the treating investigator, at immediate risk of death at the time of occurrence; i.e., it does not include a reaction that, had it occurred in a more severe form, might have caused death.
- Requires inpatient hospitalization or prolongation of an existing hospitalization (except scheduled hospitalizations for non-acute, unrelated cause such as an elective surgery)
- Results in persistent or significant disability/incapacity or any other medicinal product effects, which the doctor by his state of knowledge deemed serious
- Is a congenital anomaly/birth defect in the offspring of an exposed subject
- Is a suspected transmission of any infectious agent via a medicinal product
- Important medical events that may not result in death, be life-threatening, or require hospitalization, may be considered an SAE, when, based upon appropriate medical judgment, it jeopardizes the subject and may require medical or surgical intervention to prevent one of the outcomes listed in this definition.

Any death occurring within 30 days of the subject receiving study drug, regardless of the subject having discontinued from the study must be reported to the Lead Principal Investigator as an SAE.

ALL Serious Adverse Events MUST be reported to the Lead Principal Investigator and to the University of Chicago Comprehensive Cancer Center (UC CCC), via entry on the SAE eCRF in eVelos or paper submission via fax or email. This is whether or not they are considered related to the study agent. Refer to Section 8.3.3 for reporting guidelines.

### **8.3.2 Serious and Unexpected Suspected Adverse Reaction (SUSAR)**

A serious adverse event is considered to be a suspected adverse reaction if there is evidence to suggest a causal relationship to the study agent. This may include a single occurrence of an event strongly associated with drug exposure (e.g. Stevens Johnson Syndrome), one or more occurrence of an event otherwise

uncommon in the study population, or an aggregate analysis of specific events occurring at greater frequency than expected from historical controls.

Unexpected events are those not listed at the observed specificity or severity in the protocol, consent, Investigator brochure, or FDA package insert. This includes adverse events listed in the protocol or consent as occurring within the class of drugs or otherwise expected from the drug's pharmacological properties but which have not been previously observed with this agent.

The lead institution (University of Chicago) is responsible for notifying all participating investigators, when required, and in accordance with applicable laws and regulations of any Expedited Safety Reports that are determined by the Lead Principal Investigator to be Unexpected.

